#### Sample calculation

Before conducting this study, a sample size calculation was performed to determine the number of students required for the intervention. The calculation was based on the formula: *n* = (Z) 2 (p (1- p) e2), where *n* represents the number of participants, *Z* is set at 1.96 for a 95% confidence interval, *p* corresponds to the total number of students from 1st year of Secondary Education to 1st year of Upper Secondary Education in the target region (approximately 58,491 students in the 2024/2025 academic year), and *e* represents a 5% margin of error. Considering a potential 10% non-response rate, the minimum sample size required is 385 students.

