Teachers must meet the following inclusion criteria to participate in this study: (1) be an in-service PE teacher at the same school for the entire academic year; (2) complete the study questionnaires at three different time points; (3) not participate during the entire academic year in other intervention or training programs similar to this study; (4) attend all the training program sessions; (5) allow research team visits for classroom observation; and (6) participate in a focus group at the end of the intervention. Each PE teacher will recruit at least four classroom groups of no fewer than 16 students each, ensuring that at least 80% of the students in each group participate. Eligible students will be those aged 12–18 years from secondary schools. Participation will be completely voluntary and anonymous. School principals and students’ families will also be informed about the study’s aims and characteristics to obtain their informed consent for participation. The 80% participation rate applies only to baseline (T1); teachers not reaching it may be excluded, with replacements drawn from a waiting list. Dropout over time will not lead to exclusion if at least 60% of students complete all data points. The research team will make every effort to retain the full sample and minimize attrition throughout the study. Finally, the inclusion criteria for students’ participation in the intervention program will be: (1) obtaining consent from both parents/legal guardians and students; (2) commitment to completing the questionnaires assessing the study variables three times; and (3) regular participation in PE lessons.

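### The figure of 385 students rests on a misdefined p, leaves out the 10% non-response it claims, and cannot justify the size of a two-arm trial of 8–10 randomised teachers

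*Protocol article*

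**What the plan says.** The Sample calculation section of the protocol article reports that "a sample size calculation was performed to determine the number of students required for the intervention". It uses the usual one-proportion formula, with Z at 1.96 and e at 5 percentage points. For p, the definition given is that it "corresponds to the total number of students from 1st year of Secondary Education to 1st year of Upper Secondary Education in the target region", a count put at about 58,491. From these inputs the section draws its conclusion: "Considering a potential 10% non-response rate, the minimum sample size required is 385 students". The section names no outcome, effect size, standard deviation, power, allocation or clustering.

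The next section, on recruitment and inclusion criteria, makes the teacher the randomised unit. There are 8–10 teachers split equally, no two from the same school, with a ceiling of ten set by the team's resources. Each teacher brings at least four classes of at least 16 students, with at least 80% of each class taking part at T1. On later losses it says: "Dropout over time will not lead to exclusion if at least 60% of students complete all data points".

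The study aims compare experimental with control students at T2, and the Plan of analysis tests Time × Condition at 0.05. No proportion is estimated as a study objective.

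**The concern.** Three things are wrong with the published figure.

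- **Input.** A head count stands where the formula needs a number between 0 and 1.
- **Arithmetic.** The text says that non-response was taken into account, but the number is the one obtained without it.
- **Kind of calculation.** A margin of error for a single proportion does not bear on whether two arms of 4–5 teachers can be told apart.

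The third matters most. 385 is the only figure offered as the number of students required, and it suggests an adequacy that was never assessed. If the trial finds no difference, a reader who relies on 385 could take that as evidence of no effect, when a moderate effect might well have been missed.

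A secondary matter is that the loss the recruitment rules tolerate is larger than the 10% allowance.

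**Working it through.** **1. The plan's own figure.** Inputs from Sample calculation: Z = 1.96, e = 0.05, N = 58,491, non-response 10%. Formula: n = Z² p(1 − p)/e². The division sign and superscripts look damaged in the text at hand, and nothing here relies on that. The definition of p is a plain sentence.

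- With p as defined: 1.96² × 58,491 × (1 − 58,491)/0.05² ≈ −5.26 × 10¹², which is impossible.
- With p = 0.5 (inferred; the article does not state it): 1.96² × 0.25/0.0025 = 384.16, rounded up to **385**. This matches the published figure exactly, with no allowance.
- With 10% non-response: 384.16/0.9 = 426.8 → 427, or 385/0.9 = 427.8 → 428.
- With a finite-population correction: 384.16/(1 + 383.16/58,491) = 381.7 → 382 before the allowance, and 382/0.9 = 424.4 → 425 after it.
- For 385 to contain the allowance already, p would have to be about 0.34–0.35, a value that appears nowhere.

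**2. What the recruitment rules deliver at their minimum, in whole students.**

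| | 8 teachers | 10 teachers |
|---|---|---|
| 4 classes × 16 | 512 | 640 |
| T1 if 80% of each class of 16 takes part (13 × 4 = 52 per teacher) | 416 | 520 |
| Completers: 60% of 52 → 32 per teacher | 256 | 320 |
| Completers: 60% of 64 → 39 per teacher | 312 | 390 |

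If the 60% is applied class by class to 16 students (10 per class), the last row becomes 320 and 400. With 8 teachers the floor lies below 385 on every reading. With 10 teachers it lies below or just above, depending on the reading.

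**3. What the randomised design could detect (illustration).** The intraclass correlation (ICC) is assumed, because the article gives none. Take 51.2 students per teacher (80% of 64; using 52 changes nothing material), k = 4 or 5 teachers per arm, two-sided 0.05, 80% power, and a noncentral t on 2k − 2 = 6 or 8 degrees of freedom. In SD units, SE = √{2[ICC + (1 − ICC)/51.2]/k}. The detectable effect is 3.367 × SE for k = 4 and 3.201 × SE for k = 5.

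| ICC (assumed) | SE, k = 4 | Detectable, 8 teachers | SE, k = 5 | Detectable, 10 teachers |
|---|---|---|---|---|
| 0.02 | 0.140 | 0.47 SD | 0.125 | 0.40 SD |
| 0.05 | 0.185 | 0.62 SD | 0.166 | 0.53 SD |
| 0.10 | 0.243 | 0.82 SD | 0.217 | 0.69 SD |

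If students were independent, about 410 and 512 of them would give 0.28 and 0.25 SD.

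**The case against.** **The article is condensed, and an analysis plan may deal with power.** That would excuse silence. Here a calculation is published, and its input, arithmetic and type are wrong. No later document can turn 58,491 into a proportion or make 385 include the 10%.

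**The missing 10% may change nothing in practice.** This largely stands. If 16 per class means participants, the rules already require 512–640 students, above 428. On the 80% reading, the 8-teacher floor of 416 falls short by about 12. The first two errors alone are therefore reporting corrections.

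**The article already admits a capacity limit.** This is also true: the ceiling of ten teachers is openly put down to resources. That is a reason for the number of teachers, but it says nothing about what that number can detect.

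**The detectable effects rest on assumptions.** This stands. They use assumed ICCs and a single post-test, with no baseline adjustment and no class level. Adjusting for T1 could lower them; attrition would raise them. They also use teacher-level degrees of freedom, although the MANCOVA described in the Plan of analysis names no teacher-level term. They illustrate the order of magnitude and are not the trial's actual resolution.

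**A reader might infer more than the text supports.** One tempting reading is that 10%, 80% and 60% contradict one another. They are different quantities: anticipated non-response, a T1 participation threshold and a retention tolerance. The article also says that every effort will be made to keep the full sample. Another is that completers must fall below 385. The floors in step 2 stack several minima, each of which may be exceeded, and with 10 teachers one reading gives 39 × 10 = 390. All that can be said is that the tolerated loss exceeds the allowance and that, with 8 teachers at minimum recruitment, completers could fall below 385. Even that comparison is generous to the concern: if 385 did include non-response, the matching number of respondents would be 385 × 0.9 ≈ 347.

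**Conclusion.** The point holds. As written, the formula gives an impossible result. The published 385 is the p = 0.5 answer without the 10% that the text claims, and it should be 427–428 (about 425 with a finite-population correction). This rests on one inference, p = 0.5, which reproduces the figure exactly. The formula also answers a survey question, so 385 gives no assurance about a two-arm comparison of 8–10 teachers.

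Over assumed ICCs of 0.02–0.10, and without baseline adjustment, the detectable effect runs from about 0.40 to 0.82 SD. That compares with 0.25–0.28 SD if students could be treated as independent. The gap between tolerated loss and the 10% allowance is secondary: completers at minimum recruitment could number about 256–312 with 8 teachers and about 320–390 with 10, slightly more if the 60% is applied by class. The documents do not support calling it a contradiction, nor saying that the trial must end below 385.

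The published justification needs correcting before the trial's size is relied on.

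**What to change.** - Withdraw 385 as the justification for the trial's size, and say openly that the calculation was a one-proportion survey formula. If it is kept as a descriptive survey floor, write p = 0.5 and 428.
- State that capacity sets the size: 8–10 teachers, at least four classes each, at least 16 students per class. Say whether 16 means enrolled or participating students. That gives about 416–520 students at T1 in the first case (80% of minimum-size classes) and 512–640 in the second.
- Report the smallest detectable between-arm effect at T2 for 8 and for 10 teachers, over a stated ICC range and with 6–8 degrees of freedom. Label it as illustrative and unadjusted for baseline; the table in the working can serve.
- Say which attrition level that figure assumes. The 10%, 80% and 60% need not be merged into one number.

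The cost is a text change with no extra recruitment. The stated resolution will look less favourable, and because it assumes inference at teacher level, the text should say so, so that readers can see whether the analysis finally used matches it.

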#### Sample recruitment with inclusion criteria

Between 8–10 secondary PE teachers, assigned to the experimental group and to the control group equally, along a subset of their students, will be anticipated to take part in this study. Given the research team’s limited resources, the maximum number of participating teachers will be set at ten. Randomization will be performed using a digital tool. To minimize the risk of cross-contamination between conditions, teachers from the same high school will not participate. Teachers will be recruited through multiple channels, including social media platforms, telephone calls, and emails. Specifically, information (e.g., flyers and recruitment letters) will be shared via professional networks, PE-related social media groups, and the regional government’s official teacher registry. School principals will also be contacted directly to help disseminate the invitation within their schools.

The registration period will last approximately 2 weeks. Teachers whose participation is not approved by their school leadership will not be included. If more than 10 teachers, or multiple PE teachers from the same school, express interest, a waiting list will be created. Final selection will be based on predefined inclusion criteria and logistical feasibility, including school location, number of participants per school, schedule compatibility, and the research team’s capacity to monitor and support the intervention.

Teachers must meet the following inclusion criteria to participate in this study: (1) be an in-service PE teacher at the same school for the entire academic year; (2) complete the study questionnaires at three different time points; (3) not participate during the entire academic year in other intervention or training programs similar to this study; (4) attend all the training program sessions; (5) allow research team visits for classroom observation; and (6) participate in a focus group at the end of the intervention. Each PE teacher will recruit at least four classroom groups of no fewer than 16 students each, ensuring that at least 80% of the students in each group participate. Eligible students will be those aged 12–18 years from secondary schools. Participation will be completely voluntary and anonymous. School principals and students’ families will also be informed about the study’s aims and characteristics to obtain their informed consent for participation. The 80% participation rate applies only to baseline (T1); teachers not reaching it may be excluded, with replacements drawn from a waiting list. Dropout over time will not lead to exclusion if at least 60% of students complete all data points. The research team will make every effort to retain the full sample and minimize attrition throughout the study. Finally, the inclusion criteria for students’ participation in the intervention program will be: (1) obtaining consent from both parents/legal guardians and students; (2) commitment to completing the questionnaires assessing the study variables three times; and (3) regular participation in PE lessons.

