#### Teachers’ measures

Teachers will self-report their age, sex, teaching experience, type of school (public or private), and school location (rural or urban). It is important to note that, since some teachers’ responses may vary depending on the classroom group, teachers will need to complete the questionnaire with consideration of the specific student groups selected for the study.

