### Plan of analysis

A mixed-method analysis will be conducted to evaluate the training program, as well as to assess the impact of its implementation in PE lessons on the study variables for both teachers and students. Regarding the quantitative analysis, first, a descriptive analysis will be conducted to evaluate both teachers’ and the external researcher’s perceptions of the training program, assessing aspects such as its innovation, practical relevance, and the feasibility of the strategies implemented. Second, to assess the impact of the intervention program on the study variables for both teachers and students, the nature of the variables will first be examined through tests of normality, validity, and reliability across the three measurements. Third, the assumptions of independence, linearity, and homogeneity of variance will be verified to ensure the appropriateness of analyses based on the general linear model. Fourth, between-group and within-group differences will be analyzed using repeated-measures multivariate analysis of covariance (MANCOVA). A 3 × 2 (Time × Condition) repeated measures MANCOVA will be performed for both teachers and students, with covariates such as age, sex, teaching experience, type of school, and school location for teachers, and age, sex, sociocultural background, and school grade for students. If parametric assumptions are not met, appropriate non-parametric alternatives such as the Wilcoxon signed-rank test (for within-group comparisons) and the Mann–Whitney U test (for between-group comparisons) will be used. Subsequently, to examine intragender differences of the intervention on study variables, a 3 × 2 × 2 (Time x Condition x Sex) repeated measures MANCOVA will be performed for both teachers and students. To further examine changes in each outcome variable over time (T1, T2, and T3) within each group (experimental vs. control), multiple paired t-tests with Bonferroni correction will be conducted. Effect sizes will be calculated using partial eta squared (*η^2^ₚ*). Effect size thresholds will be interpreted as small (*η^2^ₚ* > 0.01), moderate (*η^2^ₚ* > 0.06), or large (*η^2^ₚ* > 0.14) following Cohen’s criteria. For all analyses, the significance threshold will be set at *p* < 0.05. All statistical analyses will be conducted using IBM SPSS Statistics v.25.0. Finally, a longitudinal structural equation model will be employed through the statistical software Mplus (Muthén and Muthén, 1998-2019) to analyze the predictive relationships between the study variables, allowing for the observation of potential differences at the three specific times (T1, T2, and T3) when data are collected.

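### With 8–10 teachers randomised and no balancing on school factors described, a marked split by school location or type is quite likely, and the student covariates name neither factor

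*Protocol article*

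**What the plan says.** All places are in the protocol article.

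- **Units and arms** (Sample recruitment with inclusion criteria): "Between 8–10 secondary PE teachers, assigned to the experimental group and to the control group equally", with an upper limit: "the maximum number of participating teachers will be set at ten". To limit contamination, "teachers from the same high school will not participate", which is read here as one teacher per school. Each arm therefore holds four or five schools.
- **Allocation** (same section): "Randomization will be performed using a digital tool". No stratification, matching, minimisation or constraint on school factors is described.
- **Selection** (same section): if too many teachers apply, the choice among them rests partly on "logistical feasibility, including school location, number of participants per school, schedule compatibility". School location is thus considered before the draw, but only for selecting teachers.
- **Data collected** (Teachers’ measures): teachers report "type of school (public or private), and school location (rural or urban".
- **Covariates** (Plan of analysis): one sentence names school type and location among the teacher covariates, and gives "age, sex, sociocultural background, and school grade for students". The main model for both groups is a 3 × 2 Time × Condition repeated-measures MANCOVA. Wilcoxon and Mann–Whitney tests are the fallback if its assumptions fail.

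**The concern.** With one teacher per school, school type and location are constant within a randomised unit. Thousands of student responses would not make them balance: only four or five units per arm can do that. If most rural schools, or most private ones, fall in one arm, a difference in how such schools develop over the year is mixed with the effect of the training.

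The plan itself treats these factors as relevant, because it names them for the teacher model. It does not name them for the student model, which serves the first aim. Repair in the analysis is also weak here. At school level, intercept, condition and one school factor leave 8 − 3 = 5 or 10 − 3 = 7 degrees of freedom, and a second factor leaves 4 or 6. Balance is better secured at the draw, and that cannot be done afterwards.

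**Working it through.** The article states no figure for balance at allocation, so there is none to reproduce.

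**Inputs.** From the article: N = 8 or 10 teachers, equal arms, one teacher per school, two binary school factors. Assumed: K, the number of schools of the minority type, from 2 to N/2 (larger K mirrors smaller K).

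**1. One factor.** With equal arms of m = N/2, the number x of minority-type schools in one arm is hypergeometric:

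P(x) = C(K, x) · C(N − K, m − x) / C(N, m), with C(8, 4) = 70 and C(10, 5) = 252.

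The between-arm difference is |2x − K| teachers.

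| N | K | Allocations with difference ≥ 2 | Probability |
|---|---|---|---|
| 8 | 2 | 30/70 | 43% |
| 8 | 3 | 10/70 | 14% |
| 8 | 4 | 34/70 | 49% |
| 10 | 2 | 112/252 | 44% |
| 10 | 3 | 42/252 | 17% |
| 10 | 4 | 132/252 | 52% |
| 10 | 5 | 52/252 | 21% |

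The range is 14–52%. When K is odd the difference is odd, so at least 2 then means at least 3. That is why those rows show lower probabilities but larger imbalances.

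**2. Two factors.** All allocations were enumerated for every possible overlap of the factors, counting those with a difference of at least 2 on one factor or the other.

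| N | Minority counts | Probability over overlaps |
|---|---|---|
| 8 | 4 and 4 | 49–74% |
| 8 | 4 and 2 | 66–74% |
| 8 | 3 and 2 | 43–54% |
| 10 | 5 and 5 | 21–38% |
| 10 | 5 and 3 | 29–35% |
| 10 | 4 and 4 | 52–79% |
| 10 | 4 and 2 | 68–76% |

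**3. Size of the shift.** Suppose change from T1 differs by g SD between school types, and teachers contribute equal numbers of students. An imbalance of d teachers then shifts the unadjusted contrast in change by g · d / m. The article gives no value for g; 0.2–0.5 SD is an assumption.

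- d = 2, N = 8: 0.2 × 2/4 = 0.10 to 0.5 × 2/4 = 0.25 SD.
- d = 2, N = 10: 0.2 × 2/5 = 0.08 to 0.5 × 2/5 = 0.20 SD.

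**4. What restriction achieves.** Holding one factor to a difference of at most 1 removes the risk in step 1. For a 4-of-8 factor, 36 of the 70 allocations remain. Holding two factors so leaves:

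- 18 of 70 (36 if the factors coincide or are exact opposites) for 4 and 4 of 8;
- 156–200 of 252 for 5 and 5 of 10;
- 54–120 of 252 for 4 and 4 of 10.

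If a two-sided randomisation test is wanted with 8 teachers, the smallest p with 42 allocations is 2/42 = 0.048; with 40 it is 2/40 = 0.05, which does not meet p < 0.05. A set of 42 must admit 42 − 36 = 6 splits of 3:1 for a 4-of-8 factor, or 6/42 = 14% in place of 49%. With two evenly crossed 4-of-8 factors it must admit at least 42 − 18 = 24 imbalanced allocations, 24/42 = 57%, against 52/70 = 74% with no constraint.

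**The case against.** Several points on the other side are sound, and they limit the claim.

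- **Allocation is not shown to be unrestricted.** A reader might infer simple randomisation. The article fixes equal arms, which rules out coin-flipping, and a digital tool neither states nor excludes stratification. A condensed article may leave such detail to the full protocol. What stands is that no balancing is described, although the article presents itself as a detailed, replicable account.
- **The covariate list is not closed.** It is introduced as a set of examples, so adjustment for school factors in the student model is not excluded. Sociocultural background may also capture part of a school difference. The contrast between the teacher and student lists still stands.
- **Level differences largely cancel.** A reader might infer that any rural–urban difference enters every student outcome. T1 is a level of Time, so stable differences largely drop out of the Time × Condition test; only differential change matters there. The Mann–Whitney fallback is described without covariates or T1 adjustment, so level differences could pass through in that case.
- **Chance imbalance is not bias in expectation.** That is true, and a correct cluster-level analysis would carry it in its standard errors. The student MANCOVA as described has no teacher or class term, so its standard errors would not. That is a separate issue.
- **The school mix is unknown.** Location is a selection criterion, so the mix need not be even. Hence the ranges.
- **Restriction has limits at N = 8.** Step 4 of the working shows how little room there is with two factors and a randomisation test.

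**Conclusion.** The point holds as a design weakness that should be corrected before allocation. No balancing on school factors is described for a draw of 8–10 units, and the student covariates named omit two factors that the teacher list includes. The chance of a difference of at least two teachers is 14–52% on one factor and 21–79% on at least one of two, given equal arms and the assumed mixes. The consequence for the Time × Condition test is conditional: 0.08–0.25 SD for a two-teacher imbalance if change differs by 0.2–0.5 SD between school types, which the article neither supports nor excludes. The documents do not support saying that the allocation is unrestricted, that the student model will certainly leave these factors out, or that stable differences between schools bias every student outcome.

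**What to change.** 1. Once all teachers are registered and selected, list the 70 or 252 equal-arm allocations. Draw one at random from those with acceptable balance on one or two priority factors: school location first, then school type. Do not constrain so tightly that few allocations remain.
2. Reflect the constrained factor in the student analysis, sparingly given 8–10 clusters.
3. Protect the balance after the draw. The article lets teachers who miss the 80% baseline participation rate be replaced from a waiting list. Draw after that check if timing allows; the article puts both baseline and the first training sessions in late September, so it may not. Otherwise replace a teacher with one of the same school type and location.
4. The plan names no randomisation test. If one is added with 8 teachers, keep at least 42 of the 70 allocations and accept that this only reduces the imbalance.

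Cost: a short script, all teachers registered before the draw, a rule for replacements, and a statement of the constraint in the report.

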#### Control group teachers and students

Teachers in the control group will not initially receive the training program and, consequently, will not intentionally implement any strategies aimed at supporting relatedness and class cohesion with their students. Their participation will only involve completing the questionnaires at the same time points as the experimental group teachers and students (see Figure 1). However, after the final assessment of the study, control group teachers will be invited to receive the same training program, enabling them to implement these strategies in the following academic year. A final report will also be prepared, outlining each teacher’s profile based on the teachers’ self-reports and their students’ perceptions. The training offered to control group teachers after the study will be identical in structure and content but will not involve additional data collection, as it is intended solely to offer equitable access to professional development opportunities.

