Secondly, upon completion of the training program and concurrent with the post-test (T2) administration of both teachers’ and students’ questionnaires, all experimental PE teachers will participate in a focus group. The discussions will address the following key topics: (1) the project’s theoretical underpinnings (i.e., SDT and CMC) and their feasibility within the educational setting; (2) the design and application of strategies aimed at fostering relatedness and class cohesion in PE; (3) the pedagogical approach employed (e.g., use of images, videos, practical examples, formative assessment techniques, and interactive exercises) and teachers’ perceptions of their instructional style; (4) perceived changes in the teachers’ variables assessed via questionnaires; and (5) an overall evaluation of the training program (e.g., innovation, practical relevance, feasibility of motivational strategies, intention to implement them, and overall satisfaction). The focus group session will be led by a principal moderator and an assistant, both with expertise in SDT, CMC, PE, and qualitative methods, with no trainers present to encourage open dialogue. The session will begin with an introduction to the aims and process, followed by a brief overview of the key topics. The assistant will handle logistics, take notes, and manage recordings. Finally, the moderator will summarize the main points and confirm with the teachers if the summary reflects their views or if they wish to add anything. The session will be in a neutral, comfortable setting, lasting approximately 60 min. The session will be recorded and transcribed for analysis.

Third and finally, a mixed-method evaluation will be conducted by an external researcher using the same teacher questionnaire (i.e., interaction, innovation, interest, clarity, relevance, usefulness, and feasibility), and will include external observations of the various sessions. This alignment will enable a more in-depth assessment of the training program’s quality by triangulating teachers’ self-reported perceptions with external observations.

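### Teacher inclusion criteria depend on conduct after allocation that only trained teachers can fail, and replacement at T1 is not tied to randomisation

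*Protocol article*

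**What the plan says.** All of the rules stand in the protocol article under Sample recruitment with inclusion criteria.

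- The list opens with "Teachers must meet the following inclusion criteria to participate in this study". It includes (2) completing the questionnaires at three time points and, on training, "4) attend all the training program sessions". Observation is covered by "5) allow research team visits for classroom observation", and the T2 discussion among teachers by "6) participate in a focus group at the end of the intervention".
- The 80% student participation rate applies at baseline, and "teachers not reaching it may be excluded, with replacements drawn from a waiting list".
- On later attrition: "Dropout over time will not lead to exclusion if at least 60% of students complete all data points".

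Other sections show who is affected. Control group teachers and students says of the control arm: "Their participation will only involve completing the questionnaires at the same time points as the experimental group teachers and students". Under Evaluation of the training program, "all experimental PE teachers will participate in a focus group". The Limitations section describes the fidelity observations as made on experimental teachers. Controls are offered the training only after the final assessment.

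The First group session section has experimental teachers complete their T1 questionnaires inside that session. The article gives no date for randomisation, does not say how a replacement teacher is allocated, and names no analysis set.

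**The concern.** Eligibility has to be settled before allocation if randomisation is to protect the comparison. Here several mandatory criteria describe what a teacher does in the months after allocation, and some of them exist only for the trained arm. If they are enforced, a trained teacher who skips the booster or the focus group no longer qualifies, while an equally uncommitted control teacher stays in. The trained arm is then selected for compliance and the control arm is not.

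Replacement at T1 raises a related problem. If a vacancy in a known arm is filled from a waiting list, the newcomer has not been randomised. With only 8–10 teachers, a single removal or substitution changes a large part of an arm.

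**Working it through.** The plan gives no figure on this point. Its one calculated number, 385 students, plays no part here.

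**Step 1. When each rule can be judged, and who can fail it during the trial**

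| Rule | Known at | Can be failed by |
|---|---|---|
| (2) three questionnaires | June (T3) | either arm |
| (4) all training sessions | after the January booster and the individual session that follows it | trained arm only |
| (5) observation visits | during implementation | in practice, trained arm only |
| (6) focus group | April (T2) | trained arm only |
| 80% student participation | end of September (T1) | either arm |
| 60% with all data points | June (T3) | either arm |

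**Step 2. Order of T1 and allocation.** Trained teachers fill in T1 within the first training session, so they must already have been allocated. Student T1 and the first sessions both fall in late September. The 80% check therefore appears to follow allocation, but this is an inference. If it does, a replacement who joins the trained arm after the first session has also missed a session that criterion (4) requires.

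**Step 3. How easily criterion (4) is failed.** There are 2 group sessions + 1 booster + 2 individual sessions = 5 to attend. Let s be the per-session attendance probability (assumed, with sessions and teachers independent) and k the number of trained teachers. A teacher attends all five with probability s⁵, and at least one teacher fails with probability 1 − (s⁵)ᵏ.

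| s (assumed) | s⁵ | k = 4 | k = 5 |
|---|---|---|---|
| 0.90 | 0.590 | 88% | 93% |
| 0.95 | 0.774 | 64% | 72% |
| 0.98 | 0.904 | 33% | 40% |

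The corresponding risk in the control arm is 0%.

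**Step 4. Weight of one teacher.** Equal assignment of 8–10 teachers gives 4–5 per arm, so one teacher is 1/5 = 20% to 1/4 = 25% of the arm. That teacher brings at least 4 classes of at least 16, or 4 × 16 = 64 students on the roll.

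**Step 5. Size of the bias from losing one trained teacher.** Take teacher effects as standard normal. The k effects sum to zero in expectation, so if the lowest is dropped the mean of the rest is −E(minimum)/(k − 1).

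- k = 5: 1.163/4 = 0.291 teacher-level SD.
- k = 4: 1.029/3 = 0.343 teacher-level SD.

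Multiplying by √ICC gives student SDs. The ICC is assumed, because the article gives none.

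| ICC (assumed) | √ICC | k = 5 | k = 4 |
|---|---|---|---|
| 0.05 | 0.224 | 0.065 | 0.077 |
| 0.10 | 0.316 | 0.092 | 0.108 |
| 0.20 | 0.447 | 0.130 | 0.153 |

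This is the worst case, in which the excluded teacher is exactly the one with the lowest outcomes. If compliance correlates 0.5 with outcome, the shift halves to 0.146 (k = 5) or 0.171 (k = 4) teacher-level SD, about 0.03–0.08 student SD over the same ICC range. With no correlation it is zero.

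**The case against.** The criteria can be read as undertakings. The same section says that final selection of teachers rests on predefined inclusion criteria. Criteria (1) and (3) refer to the whole academic year, so they too can be held only as promises at entry. No sentence says that a teacher who misses a session is removed. This reading is possible, but the wording works against it: the teacher criteria must be met and are phrased as attending and completing, whereas the student criterion in the same section asks only for a commitment to complete questionnaires. At best the text allows either reading, and one of them damages the trial.

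The timing argument is also open to challenge. The First group session section concerns the teachers' own questionnaire, while the 80% check concerns students, who are surveyed separately in class. The article does not order that check against allocation. This stands, which is why the order is given here as apparent rather than stated.

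The numbers are modest. At ICC 0.10, between-teacher variation alone gives a standard error for the arm difference of 0.316 × √(2/5) = 0.20 with 5 per arm, or 0.316 × √(2/4) = 0.22 with 4. The worst-case shift of 0.09–0.11 is under half of that. This also stands, but the shift is systematic rather than random, and no analysis can identify it once the teacher has gone.

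A reader might infer that less engaged classes are removed from the trained arm only. The document does not support that: the rules that act on classes, 80% and 60%, apply to both arms, as does criterion (2). Nor does it state that clusters below 60% are removed. It says only when dropout will not lead to exclusion. How the repeated-measures analysis treats students who miss a wave is a separate question and no part of this point.

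**Conclusion.** The point holds in a bounded form. Criteria (4) and (6), and in practice (5), make eligibility depend on conduct after allocation that only trained teachers can fail. Criterion (2) is also post-allocation but applies to both arms. Exclusion at 80% is discretionary, and exclusion below 60% is only implied.

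Applied as written, the rules can take out less compliant trained teachers, each 20–25% of that arm. The resulting bias is between zero and 0.29–0.34 teacher-level SD, or up to about 0.07–0.15 student SD. It is upward if the teachers lost are those with poorer results. The range rests on one lost teacher, normal teacher effects and an assumed ICC of 0.05–0.20. The chances of losing a teacher rest on assumed attendance.

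A reader might go further and say that the plan prescribes a per-protocol analysis. It does not: no analysis set is named, and a statistical analysis plan that is not shown may define one. Per-protocol describes what the comparison would become if the criteria were enforced. A later definition of the analysis set could not undo exclusions or replacements already made under them.

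**What to change.** 1. Word criteria (2), (4), (5) and (6) as agreement given at enrolment, with (4)–(6) conditional on being allocated to training. Report actual attendance, observation and focus-group participation as fidelity data.
2. Complete the 80% participation check, and any replacement from the waiting list, before teachers are randomised, and state that order.
3. State that all randomised teachers, and their students enrolled at T1, are analysed in the arm allocated, whatever the teacher's attendance or the later dropout.
4. Keep the full-attendance and 60%-completion restrictions only as labelled sensitivity analyses.

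The cost is revised wording and earlier student recruitment, so that participation is known before allocation. The statistical price is a somewhat diluted effect if a trained teacher does not comply. In return, the randomised comparison among 8–10 teachers is kept intact.
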